#### Data collection

Measurements will include face-to-face structured interviews and will be performed by trained research assistants in a quiet room in the home of the participant at baseline and at 3-months follow-up. Data collection will take about two hours per measurement. The software program Blaise Enterprise 4.7 (Heerlen, the Netherlands) will be used to directly enter data into laptop computers. Communication partners will be asked to fill in a written questionnaire at baseline and at 3-months follow-up. To measure the ability of understanding speech in noise (speech-reception-threshold in noise), a speech-in-noise test developed by Smits et al. (2013) will be included in the baseline measurements [64]. In the present study, the test will be programmed on laptop computers and performed with headphones (Speedlink Medusa). Digit triplets, uttered in Dutch, will be presented in noise. The participant will repeat the triplet he/she has heard out loud, after which the research assistant will type the digits into the laptop computer and the next digit triplet will be presented to the participant.

Three months after data collection, all participants (including non-compliant participants) will be approached for follow-up measurements.

### Outcome measures

#### DSL patient

The effects of the intervention will be evaluated in terms of hearing aid use and satisfaction, communication (primary outcomes), coping, psychosocial health and perceived quality of life (secondary outcomes) using several validated questionnaires (Table 2).

**Table 2 T2:** Measurements assessed in DSL patients and their communication partners at baseline and 3-month follow-up

	**Baseline**	**3-month follow-up**

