**Communication partners**		
*Primary outcomes*		
Coping with hearing loss (HHDI ‘reactions of others’ scale) [80]	X	X
Change from hearing aid use (IOI-HA-SO) [67]		X
Change from communication strategies (IOI-AI-SO) [67]		X_i_
Quality of life (CarerQoL) [81]	X	X
Evaluation of intervention		X_i_
*Secondary outcomes*		
Chronic fatigue (FAS) [74]	X	X
Depression (CES-D) [79]	X	X
Health (subjective health, EQ-5D) [69]	X	X
*Covariates*		
Demographic characteristics (e.g. age, gender)	X	
Relationship with patient (sort and quality of relation)	X	X
Self-efficacy (G-SES) [82]	X	X

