#### Primary outcome measures

*Difficulties with hearing aid use and maintenance* will be measured with questions on problems with hearing aid use and maintenance, e.g. “How difficult is it for you to insert your hearing aid?” or “How difficult is it for you to change your hearing aid batteries?”. Questions on *hearing aid fitting, hearing aid use and satisfaction* will be based on the Questionnaire for evaluation of hearing aid fitting, e.g. hours of hearing aid use, use of hearing aids in different situations, and appreciation of hearing aids [84]. *Self-reported change from hearing aids* is measured with the Dutch version of the widely used International Outcome Inventory for hearing aids (IOI-HA) [65,66,85]. The Communication Profile for the Hearing Impaired (CPHI) is an instrument to measure coping behavior related to hearing impairment and is divided into two domains: ‘Communication Strategies’ and ‘Personal Adjustment’ [68]. The ‘Communication Strategies’ domain of the Dutch 35-item version of CPHI will be used to measure *Communication* (coping behavior in communicative situations) and consists of three subscales: ‘Maladaptive Behavior’; ‘Verbal Strategies’ and ‘Non-verbal Strategies’ [68]. *Self-reported change from communication strategies* reported by the participant is measured with the Dutch version of the International Outcome Inventory for alternative strategies (IOI-AI) [67]. Both measures have been used for evaluation of communication programs by, e.g. Kramer et al. (2005) and Hickson et al. (2005) [41,48]).

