#### Sample size

Power calculations are based on expected progress in use of communication strategies (the Communication Strategies Scale of the Hearing Handicap and Disability Inventory), which has been the primary outcome of previous studies in persons with hearing loss [41]. In a previous RCT by Kramer et al. (2005) on the effectiveness of a home education program for older adults with hearing impairment only, the mean difference in communication skills between the intervention and control group was about 0.5 (SD = 0.8) [41]. Sample size calculations of this RCT are based on a linear mixed models and confirmed by some simulations (data not shown). Sixty-two participants per arm, with adjustment for clustering by 8 therapists in the intervention condition, provide a power of 0.80 (1-β) with alpha 0.05 (two-sided significance level), to detect a 0.5 difference between trial arms after 3 months (corrected for the differences at baseline), after taking into account a 20% dropout rate.

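### Table 2 names several unranked primary outcomes for patients and partners, while alpha 0.05 and power 0.80 are given for one communication strategies scale only

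*Protocol article*

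**What the plan says.** All places are in the protocol article.

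- **Outcome measures, DSL patient:** two patient domains are called primary: "The effects of the intervention will be evaluated in terms of hearing aid use and satisfaction, communication (primary outcomes").
- **Table 2, patients:** five primary rows. They are hearing aid fitting, use and satisfaction; difficulties with use and maintenance; IOI-HA; IOI-AI; and CPHI communication strategies. The IOI-AI is marked as assessed in the intervention group only.
- **Primary outcome measures:** the first row covers hours of use as well as "use of hearing aids in different situations, and appreciation of hearing aids". The CPHI Communication Strategies domain is described as having three subscales, and no total score is named.
- **Table 2, communication partners:** five primary rows, including "Quality of life (CarerQoL) [81"]. The IOI-AI-SO and the evaluation of the intervention are intervention-only. The HHDI scale, IOI-HA-SO and CarerQoL remain.
- **Statistical analysis:** the same family of mixed models serves all primary and secondary outcomes. No main outcome is singled out.
- **Sample size:** "Power calculations are based on expected progress in use of communication strategies (the Communication Strategies Scale of the Hearing Handicap and Disability Inventory"). The design is said to "provide a power of 0.80 (1-β") "with alpha 0.05 (two-sided significance level), to detect a 0.5 difference between trial arms after 3 months". This is the only place where a significance level appears.

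**The concern.** A primary outcome is the result on which the trial's conclusion rests. Here the label is spread over seven between-arm rows in two groups of respondents, without saying which one decides. The Discussion makes later use of the intervention depend on the trial showing it to be effective, and also lists several targets without ranking them. Read as written, a significant result on any one primary could be presented as that demonstration. The false-positive rate attached to such a conclusion would then be well above the 5% used for planning.

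The sample size fits only a trial with one primary outcome. A correction for several primaries added later would have to be paid for in power that was not planned.

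**Working it through.** **Inputs.** From Sample size: difference 0.5, SD 0.8, two-sided alpha 0.05, power 0.80, 20% dropout, 62 per arm, 8 therapists in the intervention arm. From Table 2 and Primary outcome measures: the counts below. The correlation between outcomes is not given and is assumed.

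**1. The plan's own figure.** Unclustered n per arm = 2 × [0.8 × (1.960 + 0.842) / 0.5]² = 40.2, so 41. Allowing for dropout, 41 / 0.8 = 51.25, so 52. With 62 per arm, completers are 62 × 0.8 = 49.6, which leaves a clustering factor of 49.6 / 40.2 = 1.23. With 49.6 / 8 = 6.2 completers per therapist and clustering in the intervention arm only, this corresponds to an intraclass correlation of (2 × 1.234 − 2) / (6.2 − 1) = 0.09. No intraclass correlation is stated, so 62 can be neither confirmed nor refuted, but it is plausible. It is a calculation for one outcome at the full 0.05.

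**2. Count of between-arm primary comparisons.**

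- Patients: 5 rows − 1 intervention-only = 4. With the three CPHI subscales tested separately, 4 − 1 + 3 = 6.
- Partners: 5 rows − 2 intervention-only = 3.
- Pooled: 4 + 3 = 7, or 6 + 3 = 9.

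**3. Chance of at least one false positive**, each test at two-sided 0.05, no true effect on any outcome. Independent tests: 1 − 0.95^k. Correlated tests: multivariate normal simulation with a common correlation, 600,000 draws.

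| Tests (k) | Correlation 0 | 0.3 | 0.5 | 0.7 |
|---|---|---|---|---|
| 4 (patient rows) | 18.5% | 17.4% | 15.6% | 13.1% |
| 6 (CPHI subscales separate) | 26.5% | 24.1% | 20.7% | 16.5% |
| 7 (4 + partners) | 30.2% | 27.1% | 22.9% | 17.8% |
| 9 (6 + partners) | 37.0% | 32.7% | 27.0% | 20.2% |

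With correlation 0.5 within patients and within partners but none between the two groups, 4 + 3 tests give 26.1% and 6 + 3 give 30.8%.

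**4. What a later correction would cost.** Power of 0.80 at two-sided 0.05 means the effect lies 1.960 + 0.842 = 2.802 standard errors from zero. Bonferroni over six tests has critical value 2.638 (alpha 0.0083) and power Φ(2.802 − 2.638) = 0.56. Over nine it is 2.773 (alpha 0.0056), and power is Φ(0.029) = 0.51. These are powers for one given outcome to which the planning figures apply.

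**5. Whether the powered scale is a listed primary.** The sample size uses the Communication Strategies Scale of the Hearing Handicap and Disability Inventory, with "the mean difference in communication skills between the intervention and control group was about 0.5 (SD = 0.8"). The patient primary in Table 2 is the CPHI Communication Strategies domain. The article does not say that the 0.5 and 0.8 carry over, so even the one powered outcome is not clearly among the listed primaries.

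**The case against.** The strongest case on the other side has four parts.

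- **Multiplicity rules may be in the analysis plan.** This is a condensed article, and a success rule or correction is commonly left to a document not shown. That is fair, and the absence of a correction method is not the point here. The list of primaries is fixed in this text, and it is fixed without a main one against a sample size built for one.
- **Testing each primary at 0.05 is inferred.** Alpha is stated only for the power calculation. This stands, so the rates are conditional on that use.
- **The count is open.** Table 2 has one CPHI row, and the text describes three subscales without saying that each is tested as a primary. A reader might infer at least six patient comparisons, but by rows the number is four. In the other direction, the bundled hearing-aid row could yield more than one test.
- **Patients and partners need not form one family.** They are different respondents under separate headings. Pooling them is a choice, so the two sets of rates are given separately.

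A reader might also infer that the false-positive chance is one in four or more. The figures do not support that as a floor. Four patient rows give 18.5% even if independent, six tests give about 21% at correlation 0.5, and nine fall to about 20% at 0.7.

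**Conclusion.** The concern holds in a limited form. The protocol article designates several unranked primary outcomes but gives alpha and power for one scale. The chance of at least one false primary result is about 16 to 26% for the patient set (four to six tests) and about 23 to 37% with partner outcomes pooled in (seven to nine tests). In both ranges the correlation runs from 0.5 down to 0.

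This rests on three assumptions: every primary is tested at 0.05, none has a true effect, and the correlations lie in that range. Stronger correlation lowers the figures, though at 0.7 they are still 13 to 20%. The weakness in the outcome hierarchy should be corrected; it does not show that 62 per arm is wrong.

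**What to change.** - Name one predefined patient communication strategies score as the single primary outcome. If it comes from the CPHI domain, state how the three subscales form that score, or which one is used.
- Reconcile the scale in Sample size with the primary in Table 2, and confirm that the difference of 0.5 and SD of 0.8 apply to the chosen score.
- Make the other patient measures and all partner measures secondary, reported with confidence intervals and without confirmatory claims.
- If hearing-aid use must stay confirmatory, choose one predefined measure and test it only after the communication primary succeeds, in a fixed order, so that overall alpha stays at 0.05.

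**Cost.** Hearing-aid and partner measures lose equal primary status. This is a real concession, because hearing aids are the subject of a whole chapter of the intervention and the reason for recruiting hearing-aid owners. Sample size and data collection do not change. The stated power of 0.80 holds only if the planning figures apply to the chosen score. If they do not, the calculation has to be repeated for that score.

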**DSL patients**		
*Primary outcome measures*		
Hearing aid fitting, hearing aid use and satisfaction	X	X
Difficulties with hearing aid use and maintenance	X	X
Change in hearing aid use (IOI-HA) [65,66]		X
Change from communication strategies (IOI-AI) [67]		X_i_
Communication (CPHI-communication strategies) [68]	X	X
*Secondary outcomes*		
Health (subjective health)	X	X
Health related quality of life (EuroQol-5 Dimensions (EQ-5D)) [69]	X	X
Coping with hearing impairment (CPHI-personal adjustment) [68]	X	X
Vision-related quality of life (LVQOL) [70,71]	X	X
Loneliness (Loneliness scale) [72,73]	X	X
Fatigue (FAS) [74]	X	X
Participation (parts of D-AI-interpersonal interactions and relationships) [75]	X	X
Autonomy (PAQ) [76]	X	X
Evaluation of intervention		X_i_
*Covariates*		
Patient characteristics (e.g. age, gender, education, living arrangement)	X	
Disability characteristics (eye condition, VA, self-perceived vision (VFQ25-general vision subscale [77]), hearing condition, hearing loss (speech-reception-threshold in noise))	X	
Cognition (6-item screener MMSE) [78]	X	
Depressive symptoms (CES-D) [79]	X	X
Major life events between baseline and follow-up		X

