**Costs**		
Healthcare use (iMCQ) [83]	X	X
Intervention costs (occupational therapists, travel costs, time communication partner)		X_i_
Costs informal care (SF-HLQ, time spent on care for communication partner)	X	X
Proxy: Travel time and expenses	X	
Proxy: Time spent on care giving for communication partner	X	X

X_i_ Assessed in intervention group only.

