#### Statistical analysis

Data will be analyzed according to the intention-to-treat principle. Linear mixed models for continuous outcomes and generalized linear mixed models for counts and categorical outcomes will be used to assess treatment effects with respect to primary and secondary outcome measures. Treatment effects will be assessed according to the analysis strategy as described by Winkens et al. [87-89] and is defined as the treatment allocation*time interaction. To account for correlatedness of outcomes within the same therapist, a random intercept for therapist is included in the model.

For participants who are not treated according to the protocol, intention-to-treat analyses will be compared to per-protocol analyses. Data will be analyzed using the software package SPSS 20 for Windows.

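### The stated allocation-by-time effect cannot be estimated for 2 of 5 patient primaries and 3 of 5 partner primaries, and three of these five have no control-arm data at all

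*Protocol article*

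**What the plan says.** The Statistical analysis section states that linear and generalised linear mixed models "will be used to assess treatment effects with respect to primary and secondary outcome measures", with a random intercept for therapist. The effect "is defined as the treatment allocation*time interaction". No outcome is exempted.

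Table 2 lists five primary outcomes for patients and, in a separate block, five for communication partners. Among the patient primaries, "Change in hearing aid use (IOI-HA) [65,66" is marked at 3 months only. "Change from communication strategies (IOI-AI) [67" is also at 3 months only and carries the X_i mark, which the footnote explains as "Assessed in intervention group only". Among the partner primaries, IOI-HA-SO is marked at 3 months only, while "Change from communication strategies (IOI-AI-SO) [67" and the evaluation of the intervention are X_i. The patient version of that evaluation is also X_i, but it sits in the secondary list.

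The label is not a slip confined to the table, at least for patients: the section headed Primary outcome measures describes both IOI-HA and IOI-AI. For partners, the text section does not separate primary from secondary outcomes, so their status rests on Table 2 alone.

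**The concern.** An allocation-by-time interaction compares the change over time in one arm with the change in the other. It needs values from both arms at both visits. The article fixes that definition for every primary and secondary outcome and, in the same article, fixes a collection schedule that cannot supply it for several of them.

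Two different things are at stake. For the one-arm measures, a primary outcome of a randomised trial would have no comparator. The Discussion concedes that participants and therapists are unblinded and that contact with a sympathetic professional may by itself produce reported change. It defines the effect of the intervention as the difference between the groups. Ratings given only by treated participants or their partners contain no such difference, so a favourable score could not be attributed to the intervention. For the measures taken in both arms at follow-up only, the comparison is sound but the published definition of the effect does not fit.

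**Working it through.** **Inputs.** The definition of the effect comes from the Statistical analysis section. The collection marks come from Table 2 and its footnote.

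**Step 1: class each primary row.**

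| Block | Primary outcome | Baseline | 3 months | Arms |
|---|---|---|---|---|
| Patient | "Hearing aid fitting, hearing aid use and satisfaction" | X | X | both |
| Patient | "Difficulties with hearing aid use and maintenance" | X | X | both |
| Patient | IOI-HA | none | X | both |
| Patient | IOI-AI | none | X_i | intervention only |
| Patient | CPHI communication strategies | X | X | both |
| Partner | HHDI reactions of others | X | X | both |
| Partner | IOI-HA-SO | none | X | both |
| Partner | IOI-AI-SO | none | X_i | intervention only |
| Partner | CarerQoL | X | X | both |
| Partner | Evaluation of the intervention | none | X_i | intervention only |

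**Step 2: ask what each pattern can estimate.** With g = 1 for intervention and t = 1 for 3 months, the fixed part of the stated model is

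E(Y) = b0 + b1·g + b2·t + b3·g·t,

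and the stated effect is b3 = (mean at g=1,t=1 − mean at g=1,t=0) − (mean at g=0,t=1 − mean at g=0,t=0). Four cell means are needed. For non-linear outcomes the same holds on the scale of the linear predictor.

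- Both arms, both visits: design rows (1,0,0,0), (1,0,1,0), (1,1,0,0), (1,1,1,1). The rank is 4 of 4, so b3 is estimable.
- Both arms, follow-up only: rows (1,0,1,0), (1,1,1,1). The rank is 2 of 4. Only b0 + b2 and b1 + b3 are identified, so b3 alone is not. The between-arm difference at 3 months, b1 + b3, is identified and is a valid randomised contrast.
- Intervention arm, follow-up only: row (1,1,1,1). The rank is 1 of 4. No contrast between arms of any kind is identified.

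The therapist random intercept does not change these ranks, because it supplies no missing cell.

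**Step 3: count.**

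- Patients: 1 intervention-only + 1 without baseline = 2 of 5; 3 of 5 can take the stated analysis.
- Partners: 2 intervention-only + 1 without baseline = 3 of 5; 2 of 5 can take it.
- Across both blocks: 3 + 2 = 5 rows of 10. All five lack a baseline; three of them also lack a control arm.
- In addition, one patient secondary outcome (evaluation of the intervention) is intervention-only.

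**Step 4: check whether the sample size is touched.** The Sample size section gives 62 per arm, based on communication strategies with a difference of 0.5 and SD 0.8. Without clustering these inputs give 41 per arm, or 41/0.8 = 51.25, rounded up to 52, after 20% dropout. The 62 therefore leaves room for therapist clustering. It cannot be reproduced exactly because no intraclass correlation is given. None of the five rows above enters this calculation, and the communication domain on which it rests is measured in both arms at both visits through the CPHI.

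**The case against.** The strongest reply is that the main patient question is intact. The article names hearing aid use and satisfaction, and communication, as the primary patient domains. Each has at least one measure taken in both arms at both visits, and the sample size rests on communication strategies. That stands, and it limits the severity.

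Second, IOI-HA and IOI-HA-SO ask respondents to report change themselves, so the arm difference at 3 months is the natural counterpart of an interaction, and an analysis plan that is not shown may say so. That also stands: for these two the published sentence is imprecise and no necessary data are missing. A reader might infer that they give no randomised evidence, or that the analyst will have to invent a method after seeing the data. The documents support neither inference.

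Third, untreated controls cannot sensibly rate an intervention or strategies they have not been taught, and the footnote discloses the one-arm collection openly. This explains why the data are one-armed; it does not make them primary outcomes of a randomised comparison. An unseen analysis plan cannot supply control values that are not collected.

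A reader might also infer that half of the trial's primary evidence is lost. The 5 of 10 arises only by pooling two populations that Table 2 lists separately, and only three rows lack a comparator. Nor do the documents say that one-arm ratings will be presented as proof of effectiveness; their labels merely leave that open.

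**Conclusion.** The point holds within these limits. The stated effect cannot be estimated for 2 of 5 patient primaries and 3 of 5 partner primaries. Three of these rows (patient IOI-AI, partner IOI-AI-SO, partner evaluation of the intervention) permit no randomised comparison and should not be primary effectiveness outcomes. The patient evaluation has the same defect as a secondary outcome, and its different rank in the two blocks is itself inconsistent. IOI-HA and IOI-HA-SO keep a valid randomised comparison at 3 months and need only a definition that fits.

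The remaining five primaries, the sample size and the randomisation are unaffected. The conclusion assumes that the marks in Table 2 show the schedule as intended; the footnote and the nature of the one-arm questions support this. This should be fixed, but it does not undermine the trial.

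**What to change.** 1. Move patient IOI-AI, partner IOI-AI-SO and the partner evaluation of the intervention out of the primary lists, and the patient evaluation out of the secondary list. Report all four descriptively, as process measures in the intervention arm.
2. State that IOI-HA and IOI-HA-SO are analysed as the between-arm difference at 3 months, keeping the therapist random intercept. Adjust IOI-HA for baseline hearing aid use and satisfaction, which Table 2 already collects. The documents give no basis for choosing a particular baseline covariate for IOI-HA-SO.
3. Restrict the allocation-by-time definition to outcomes measured in both arms at both visits.

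The cost is rewording of Table 2, the outcome sections and the Statistical analysis section. No patients, visits or questionnaire items are added. The downside is that three measures lose the label of primary and one loses the label of secondary.
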